#### **Missing Data**

Missing data mechanisms are explored and reported.

Missing data across and between intervention arms are reported and compared.

The RCT is intent-to-treat from randomisation. All randomised cases with any missing data will be included in the analyses of PTSD and MDD diagnoses and secondary outcomes (linear mixed effects models are considered to be reasonably robust to missing data at random).

Sensitivity analyses for the primary trial objectives will be carried out to test robustness of the results to any missing data mechanism.

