### 11.2 The Number of Participants

We plan to recruit 570 participants.

The risk of student paramedics developing full syndromal PTSD and MD over two years without intervention is 10% (1), and 25% if subsyndromal PTSD and MD that cause significant distress are included. We predict that our intervention will reduce the relative risk by 50%. Setting power at 80%,  $\alpha=.05$  and hypothesizing a reduction of relative risk of 50% gives an odds ratio of 0.429, which requires a total sample size of N=304 to show a risk reduction of 50% between the active and placebo intervention. Thus, each condition would require N=152. Since we have a third condition (no-training control), the total sample size required would be N=456. Allowing for a 20% rate of attrition, we will require a total sample size of N=570.

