### 11.3 The Level of Statistical Significance

Significance levels were set at  $p < .05$ .

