## **Randomisation and Blinding**

Participants are randomised on a 1:1:1 ratio as per a computer-generated randomisation schedule by OCTRU (Oxford Clinical Trials Research Unit) stratified by site, gender and baseline PHQ-9 score ( $\geq 9$  vs.  $< 9$ ) and PCL-5 score ( $\geq 33$  vs.  $< 33$ ). The researchers inform participants of the intervention they are to receive after participants have completed baseline assessments. Outcome assessment is single blind. Online questionnaires throughout the intervention and follow-up time points are completed without any involvement of the researchers. The clinical interview is done by an independent assessor, who is blind to treatment allocation. All personnel involved in the blood and saliva samples are blinded to intervention allocation. Due to the nature of the interventions, participants cannot be completely blinded to allocation.

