## **STATISTICAL PRINCIPLES**

### **Statistical Significance and Multiple Testing**

In the case of different scaling, continuous variables are standardized for the analysis. Global comparisons are tested and if significant, group comparisons are then carried out.

[name], [name], [name], [name], [name], [name], [name], [name], [name], [name], [name], & [name] Cognitive resilience training to prevent PTSD and MDD in paramedics: A randomised controlled trial.

If not specified otherwise, one or the other, main effects of intervention group or interaction effects between intervention group and time in favour of iCT-R, indicate intervention superiority.

All analyses will be carried out with a significance level of  $p < .05$ , two-sided.

No adjustments for multiple testing are made, as the primary trial objective is to evaluate any superiority in efficacy of the new resilience intervention compared to the existing online intervention (group comparison between these two groups of highest priority and directive hypothesis).

Confidence intervals are reported at the 95% level, two-sided.

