Measures to test the tertiary trial objective are risk factors and predictors at baseline, such as level of social support (adapted from a brief measure of social support), trauma exposure (trauma screener), demographic data (general information questionnaire), neuroticism as a personality factor (subscale neuroticism from the Eysenck Personality Questionnaire), level of concrete thinking (CAT), and frequency, duration, and distress with regards to intrusive memories (Intrusions Questionnaire).

More information on the outcome measures can be found in the published trial protocol ([name] et al., 2018).

Time points:

Data are collected at pre-intervention, post-intervention, at 6-months follow-up, at 1-year follow-up and at 2-years follow-up. PTSD and MDD diagnoses are assessed pre-intervention, post-intervention, at 1-year and at 2-years follow-up, PTSD and MDD symptom severity are assessed at all measurement points. Secondary outcome measures are assessed at pre-intervention, post-intervention, and at 1-year and at 2-years follow-up. All measures for the tertiary trial objective are assessed at pre-intervention, at 1-year and at 2-years follow-up. All tertiary measures (except for demographics) are assessed at post-intervention, and trauma exposure, concrete thinking and intrusion measures are collected at 6-months follow-up, as well.

For the early analysis of the trial results, 1-year follow-up is the short-term primary outcome time point. Once the trial has been completed, the primary outcome time point is 2-years follow-up as described in the published trial protocol.

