## **Analysis Methods**

Analyses of the primary trial objectives:

To analyse any differences between the intervention arms in terms of effectiveness with regards to rates of PTSD and MDD diagnoses (SCID-5) at 1-year follow-up (short-term primary outcome time point) and at 2-years follow-up (long-term primary outcome time point once completed), intervention condition and the interaction between intervention time and

intervention group on rates of PTSD and MDD diagnoses, logistic mixed effects models with PTSD and MDD diagnoses as outcomes (short-term outcome 1-year follow-up data, long-term outcome 2-years follow-up once completed) are specified and analysed.

To analyse any differences between the intervention arms in terms of effectiveness with regards to PTSD symptom severity (PCL-5) or MDD symptom severity (PHQ-9) at 1-year follow-up (short-term primary outcome time point) and at 2-years follow-up (long-term primary outcome time point once completed), intervention condition (categorical; iCT-R versus Mind-Online versus Standard practice; level 2) and the interaction between intervention time (categorical; post-intervention, 6-months follow-up; 1-year-follow-up, 2-year follow-up, once completed; level 1) and intervention group on PTSD or MDD symptom severity, linear mixed effects models with either PTSD or MDD symptom severity as outcomes are specified and analysed.

Both repeated assessments and intervention arm are specified as categorical variables for reasons of flexibility in the modelling approach. Repeated assessments/ time, intervention arm, both their interaction effects, and baseline scores and covariates are estimated as fixed effects and random effects are estimated for time (level 1) nested within the participants (level 2). An unstructured variance-covariance matrix is used to model the error correlation structure within the participants. Estimation method is Maximum Likelihood. Normality of the residuals for the outcomes is confirmed visually.

Randomisation has been done by stratification by site, gender, and baseline PTSD symptom severity and MDD symptom severity. Therefore, baseline PTSD symptom severity and MDD symptom severity and randomisation factors are added as covariates in these models. Site is added as random factor in those models. If non-significant, they will not be carried forward into further analyses.

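### The SCID diagnosis model uses PCL-5 and PHQ-9 only at baseline, and the imputation planned as a sensitivity analysis does not say that follow-up scores will inform missing diagnoses

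*Combined protocol and SAP*

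**What the plan says.** SAP 6.1 makes SCID-5 diagnoses of PTSD and MDD the primary outcome measure. SAP 6.2 analyses them with "logistic mixed effects models with PTSD and MDD diagnoses as outcomes". The covariates are baseline PTSD and MDD symptom severity and the randomisation factors, with site as a random effect. Post-baseline PCL-5 and PHQ-9 scores appear only in their own linear mixed models.

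SCID interviews are scheduled at baseline and at 6, 52 and 104 weeks (SAP 6.1, Protocol Appendix B). By contrast, "PTSD and MDD symptom severity are assessed at all measurement points", which adds 24 weeks. The two sources are collected separately. Under SAP 3.2, "Online questionnaires throughout the intervention and follow-up time points are completed without any involvement of the researchers", whereas the interview needs an independent blinded assessor.

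On missing data, SAP 6.3 says: "All randomised cases with any missing data will be included in the analyses of PTSD and MDD diagnoses and secondary outcomes". It supports this by the robustness of linear mixed models to data missing at random. SAP 6.4 then lists three sensitivity analyses for the diagnosis result: including cases with missing data, adding covariates that predict missingness, and imputation. No variables, imputation model or number of imputations are given.

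**The concern.** At the one-year analysis, a participant without a 52-week SCID informs the result only through baseline covariates and the 6-week SCID. Once two-year data are added, a 104-week SCID can contribute too. A participant with no follow-up SCID at all has no outcome in the likelihood, so the SAP 6.3 statement about including all randomised cases cannot hold for that person. The justification there also refers to linear models, although the diagnosis model is logistic.

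The trial may hold PCL-5 and PHQ-9 scores for some of these people. Those scores bear more directly on the missing diagnosis than a 6-week interview does. If interviews are missed for reasons related to current symptoms, and this differs by arm, the odds ratio is distorted. Even if it does not, some information is left unused.

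SAP 6.4 could make use of the scores but does not say so. The obvious predictors of a missed interview are follow-up symptom scores. Entering these as covariates would adjust for post-randomisation outcomes and remove part of the treatment effect being estimated.

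**Working it through.** **Inputs from the documents.** Alpha 0.05 (Protocol 11.3), two-sided (SAP 4.1: "Confidence intervals are reported at the 95% level, two-sided"); power 80%, 50% relative reduction and 20% attrition (Protocol 11.2, SAP 3.3). The control risk over two years is "25% if subsyndromal PTSD and MD that cause significant distress are included". One-year pooled rates are 8.7% PTSD and 15.8% depression (SAP 3.5).

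**Inputs assumed, because the documents do not give them.** Share of interview-missers who return a questionnaire: 25% to 100%. Strength of the score-diagnosis association: R² 0.3 to 0.5 for precision, latent correlation 0.6 to 0.8 for bias.

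**1. The plan's own figure.** With p1 = 0.25, p2 = 0.125 and mean 0.1875:

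n = [1.960·√(2·0.1875·0.8125) + 0.842·√(0.25·0.75 + 0.125·0.875)]² / 0.125² ≈ 152 per arm.

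Then 2 × 152 = 304, 3 × 152 = 456, 456/0.8 = 570, and OR = (0.125/0.875)/(0.25/0.75) = 0.429. All of these match the plan. Each arm randomises 190, of whom 152 are expected to have data and 38 not.

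**2. Precision.** If a share q of the 38 missers have a usable score, the variance per arm is proportional to R²/(152 + 38q) + (1 − R²)/152. The reciprocal is the effective n.

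| q | R² | Effective n | SE change | Power |
|---|---|---|---|---|
| 0 | – | 152 | 0 | 80.0% |
| 0.25 | 0.3 | 1/(0.3/161.5 + 0.7/152) = 154.7 | −0.9% | 80.7% |
| 0.5 | 0.5 | 1/(0.5/171 + 0.5/152) = 160.9 | −2.8% | 82.2% |
| 1 | 0.5 | 1/(0.5/190 + 0.5/152) = 168.9 | −5.1% | 84.0% |

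The ceiling, with all 190 interviewed, is 88.0%. At 30% loss the corresponding change is from 74.5% to between 75.8% and 81.2%. Lower prevalence weakens the association: a latent correlation of 0.8 gives R² of about 0.42 at 25% prevalence but 0.35 at 8.7%; a correlation of 0.6 gives 0.21 and 0.15. With R² = 0.15, effective n is only 153.4 to 156.7 and power 80.4% to 81.2%.

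**3. Bias.** Large-sample simulation: diagnosis is a threshold on latent severity, the score is correlated 0.6 or 0.8 with it, and 20% of interviews are missing per arm. The log-odds of missing rise by 0, 0.5 or 1 per SD of score. True OR 0.429.

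| Missingness depends on score in | Observed SCID only | Plus 6-week SCID | Plus score, all missers |
|---|---|---|---|
| Neither arm | 0.43 | 0.43 | 0.43 |
| Both arms equally | 0.40–0.42 | 0.40–0.42 | 0.43 |
| iCT-R only | 0.30–0.38 | 0.31–0.39 | 0.43 |
| Mind-Online only | 0.48–0.57 | 0.47–0.55 | 0.43 |

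The 6-week SCID recovers little. The last column is a best case: every misser has a score, and missingness depends on that score alone.

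**4. When only half of the missers have a score.** Take the strongest iCT-R-only case, with an observed rate of 9.0% against a true 12.5%. The missers' rate is (12.5 − 0.8 × 9.0)/0.2 = 26.5%. If half are imputed at 26.5% and half at 9.0%, the arm's rate is 7.2 + 2.65 + 0.9 = 10.75%. The OR is then (0.1075/0.8925)/(0.25/0.75) = 0.361, compared with 0.297 from observed SCIDs and a true 0.429. About half of the log-OR bias is removed. A separate finite-sample simulation at 190 per arm, also run at rates near the one-year rates, gave a reduction of roughly 40 to 50%. With dropout unrelated to symptoms it gave a 1 to 4% fall in the SD of the log OR.

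**5. Cases available to an imputation model.** At 152 per arm: 0.087 × 152 ≈ 13 PTSD cases and 0.158 × 152 ≈ 24 depression cases, using pooled rates.

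**The case against.** The strongest reply is that the SAP already plans the remedy: 6.3 promises to explore missing-data mechanisms, and 6.4 lists predictors of missingness and imputation. The mixed model and the imputation both rest on missing at random, so which one is called primary is partly preference. This stands to the extent that the plan cannot be said to ignore the problem. It does not settle the point, because the imputation as described could be run without a single follow-up score, and the covariate option is open to post-randomisation variables.

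A reader might infer that the model runs on SCID records alone. It does not: baseline PCL-5 and PHQ-9 are covariates, and other SCID visits contribute. Nor does anyone miss a 24-week interview, since none is scheduled; the 24-week score matters as a predictor of the 52-week diagnosis.

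The size figures also favour the change. They use 25% against 12.5%, a two-year risk that includes subsyndromal cases, whereas the model analyses diagnoses, first at one year. Protocol 8.5 places questionnaires on the same occasions as interviews, so how many interview-missers return a form is unknown.

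Two costs are real. About 13 PTSD cases per arm is thin for a fully within-arm imputation model with many predictors. And the scores are self-reports from participants who know their allocation, used to fill in a blinded outcome.

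**Conclusion.** The point holds as a concrete, low-cost improvement to the handling of missing diagnoses. The primary model conditions only on baseline covariates and other SCID visits, people with no follow-up SCID drop out of it despite SAP 6.3, and SAP 6.4 does not commit to using the follow-up scores.

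A reader might go further and conclude that the primary odds ratio is biased, or that the scores would remove the bias. The documents support neither. Bias requires missingness related to symptoms beyond what is modelled, and it is material for the odds ratio mainly when that relation differs by arm; with an equal relation the OR moves only to 0.40–0.42. The scores help only for people who return a questionnaire, and only if missingness is at random given those scores.

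The gain in precision is modest: 80.0% power to between 80.7% and 84.0% at the planned 20% loss with R² of 0.3 to 0.5, and less if the association is weaker. All these sizes rest on assumed return rates and score-diagnosis associations.

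**What to change.** Before unblinding, specify multiple imputation of missing SCID diagnoses.

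- **Imputation model:** arm, baseline covariates, other SCID results, and PCL-5 and PHQ-9 at 6, 24 and 52 weeks (and 104 once available). Include arm interactions, or impute within arm where case numbers allow. Use penalisation or similar protection against separation.
- **Analysis model:** pre-randomisation covariates only.
- **SAP 6.4:** restrict the second sensitivity analysis to pre-randomisation covariates.
- **Reporting:** present the result beside the un-imputed mixed model, either as the primary analysis or, at minimum, as the named content of the imputation item in SAP 6.4.
- **SAP 6.3:** state that participants with no follow-up SCID do not contribute to the un-imputed diagnosis model, and report by arm how many interview-missers have scores.

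No new data or visits are needed. The costs are extra analysis work, an imputation model that must cope with few cases, and reliance on unblinded self-report to inform missing blinded diagnoses; the last should be stated as a limitation.

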#### **Sensitivity Analysis**

Sensitivity analyses will be carried out for the analyses of the primary trial objectives. We will test whether any intervention superiority or non-inferiority with regards to PTSD and MDD diagnoses is robust/ holds when 1) analysing data including cases with missing data, 2)

[name], [name], [name], [name], [name], [name], [name], [name], [name], [name], [name], & [name] Cognitive resilience training to prevent PTSD and MDD in paramedics: A randomised controlled trial.

analysing data including any potential covariates that are predictive of any missing data, and  
3) imputation.

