Additional missing data explorations are reported. Any missing data, withdrawal from the intervention, or loss to follow-up are reported in tables for the whole sample and by intervention groups based on the Covid status variables for the short-term primary outcome time point 1-year follow-up and the 2-year follow-up assessment point, once completed (means and standard deviations for continuous outcomes, absolute numbers and percentages for dichotomous outcomes).

In the case of any missing data, withdrawal, or loss to follow-up dependent on Covid status or the endorsement of the COVID questions, additional sensitivity analyses need to be carried out.

CACE analyses:

In the case of potential intervention heterogeneity due to any influence of the Covid pandemic, additional CACE analyses are carried out, as well, to test whether Covid status or questions had an influence on compliance to the interventions. In case of any differences the Covid CACE is compared with the intent-to-treat intervention effects resulting from the primary trial analyses and results are reported.

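### The missing-data sensitivity analyses do not deliver the robustness the SAP promises: one repeats the primary analysis, one assumes missing at random, and the imputation is unspecified

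*Combined protocol and SAP*

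**What the plan says.** SAP, Missing Data, sets the primary handling: "All randomised cases with any missing data will be included in the analyses of PTSD and MDD diagnoses and secondary outcomes". The reason given is that "linear mixed effects models are considered to be reasonably robust to missing data at random". The section adds that mechanisms will be explored and missingness compared between arms. It then states the aim: "Sensitivity analyses for the primary trial objectives will be carried out to test robustness of the results to any missing data mechanism".

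SAP, Sensitivity Analysis, lists three checks on the diagnosis result:

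1. "analysing data including cases with missing data";
2. "analysing data including any potential covariates that are predictive of any missing data";
3. imputation, a single word with nothing further.

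SAP, Supplementary/Additional Analyses, provides that if missingness, withdrawal or loss to follow-up depends on Covid status or the Covid questions, "additional sensitivity analyses need to be carried out". No method is given there either.

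SAP, Analysis Methods, puts baseline scores into the models as covariates. For the symptom-severity models it lists the time levels as post-intervention, 6 months, 1 year and later 2 years. It does not list the time levels for the diagnosis model.

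**The concern.** The primary outcome is a PTSD or MDD diagnosis made at interview. Being unwell is itself a plausible reason to miss that interview. Contact also differs by arm: the two online arms get coaching and reminders, and Standard Practice gets no online support. The only payment mentioned (Protocol 14.6) comes at 104 weeks, after the 1-year interview.

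A sensitivity set should therefore show how far the missing-at-random assumption must fail before the conclusion changes. The SAP promises something of that kind but names no analysis that does it. The 1-year analysis was brought forward because a favourable result could support early roll-out (SAP, Timing of Final Analysis), so readers will want to know how much the result depends on people who were not assessed. Leaving the imputation open also means its model could be chosen after results are known.

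**Working it through.** **Step 1: each listed analysis against the stated aim.**

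| Listed analysis | What it assumes | What it adds to the primary analysis |
|---|---|---|
| 1. Include cases with missing data | Missing at random | Nothing: Missing Data already includes them |
| 2. Add predictors of missingness | Missing at random, given more covariates | A wider set of covariates |
| 3. Imputation | Not stated | Cannot be judged |
| Covid-related, conditional | Not stated | Cannot be judged |

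No delta-adjusted, reference-based, pattern-mixture, selection-model or tipping-point analysis appears in either document.

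**Step 2: who enters the likelihood.** With baseline as a covariate and only post-baseline visits as outcomes, a participant with no follow-up has no outcome row. The symptom models are set out this way. If the diagnosis model has the same structure, such participants add nothing to the likelihood and enter only through imputation.

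**Step 3: reproduce the plan's design figure.** Inputs from Protocol 11.2: control risk p₁ = 0.25, 50% relative reduction so p₂ = 0.125, power 80%, α = 0.05 (two-sided per the SAP).

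- OR = (0.125/0.875)/(0.25/0.75) = 0.429, as stated.
- n per arm = [1.960√(2 × 0.1875 × 0.8125) + 0.842√(0.25 × 0.75 + 0.125 × 0.875)]² / 0.125² = 151.9, so 152. Two arms 304; three arms 456; 456/0.8 = 570. All match.
- Per arm: 570/3 = 190 randomised, 152 observed, 38 missing.

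**Step 4: an illustrative tipping point, iCT-R against Mind-Online.** Assumptions: 20% missing in each arm; observed 19/152 (12.5%) and 38/152 (25%); missing Mind-Online participants keep the 25% risk; only iCT-R dropout is informative; intermediate visits ignored. Observed cases alone give p = 0.005.

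Let k be the odds of diagnosis in missing iCT-R participants divided by the odds in those observed. The risk in the missing is r = 0.125k/(0.875 + 0.125k). The overall iCT-R risk is 0.8 × 0.125 + 0.2r, compared with 25% on 190 per arm by uncorrected chi-square.

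| k | r | iCT-R risk | Difference (points) | p |
|---|---|---|---|---|
| 1 | 12.5% | 12.5% | −12.5 | 0.002 |
| 2 | 22.2% | 14.4% | −10.6 | 0.010 |
| 2.33 | 25.0% | 15.0% | −10.0 | 0.015 |
| 3 | 30.0% | 16.0% | −9.0 | 0.030 |
| 4 | 36.4% | 17.3% | −7.7 | 0.065 |

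The 25% row is 0.8 × 0.125 + 0.2 × 0.25 = 0.15, RR = 0.15/0.25 = 0.60, z = 0.10/√(2 × 0.20 × 0.80/190) = 2.44.

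In whole counts, with 10 events among the missing Mind-Online participants (48/190): 13 of 38 missing iCT-R participants diagnosed gives 32/190, p = 0.044; 14 of 38 (36.8%) gives 33/190, p = 0.060.

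**Step 5: a caution on these p-values.** They treat filled-in values as observed, so they are too small. With k fixed, the iCT-R standard error is that of 152 observed cases multiplied by f = 0.8 + 0.2k/(0.875 + 0.125k)².

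- k = 2.33: f = 1.143; SE of the difference = √(1.143² × 0.1094/152 + 0.1875/152) = 0.0466; z = 0.10/0.0466 = 2.14; p = 0.03.
- k = 3: f = 1.184; SE = 0.0474; z = 0.09/0.0474 = 1.90; p = 0.06.

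So a proper imputation would tip at just under 3 rather than between 3 and 4.

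**The case against.** The best defence is that imputation is in the plan and nothing confines it to missing at random. A delta-adjusted or reference-based version would fit the single word used. That stands: the third analysis is unspecified, and the documents do not say that it rests on missing at random. The SAP also uses the word any loosely, so its promise may only mean whatever mechanism is found. Even so, none of the listed analyses is tied to a mechanism other than missing at random.

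Three stronger readings are tempting and are not supported.

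- *All listed analyses must agree.* This is certain only for the first. PCL-5 and PHQ-9 are completed online, separately from the interview, and also at 24 weeks. If unwell participants score high before missing an interview, the second and third analyses could move the estimate.
- *Informative dropout would go undetected because of this plan.* Observed data cannot identify it under any plan. A sensitivity analysis shows how much of it the conclusion can bear. Differential missingness would be visible to readers, since the SAP reports it by arm.
- *The intent-to-treat statement is false.* The time levels of the diagnosis model are inferred, and imputation is planned. Someone who misses week 52 may have a 6-week interview and would contribute to a repeated-measures model. The documents do not say how many participants have no follow-up at all.

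The justification in Missing Data speaks of linear models while the diagnoses use logistic ones. That is a wording gap: likelihood-based logistic models can also be valid under missing at random.

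**Conclusion.** The point holds. Followed as written, the plan does not deliver its own aim: one analysis is redundant, one stays within missing at random, one is undefined, and no departure from missing at random is named.

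The illustration does not suggest that the trial's conclusion is fragile. At the design effect, giving missing iCT-R participants the control risk leaves the result significant. It takes odds of diagnosis about 3 to 4 times those observed to lose significance, or just under 3 once imputation uncertainty is counted. What is missing is any planned analysis that would tell the reader this.

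The figures are not a forecast. They use two-year rates that include subsyndromal cases, whereas the SAP's first analysis is of diagnoses at 1 year, with pooled rates of 8.7% for PTSD and 15.8% for depression. The values of k and the restriction of informative dropout to iCT-R are assumptions.

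This should be changed. It does not invalidate the primary analysis.

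**What to change.** In SAP, Sensitivity Analysis, replace the first analysis and define the third:

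- Multiple imputation by arm of missing SCID diagnoses for all randomised participants. Auxiliaries are PCL-5 and PHQ-9 at baseline, 6, 24 and 52 weeks. Add 104 weeks only for the 2-year analysis, because those data are not complete at the 1-year analysis.
- From those imputations, a delta-adjusted tipping-point analysis on the log-odds of diagnosis, with delta varied separately by arm over a range justified in advance. Report the delta at which the conclusion changes.
- Optionally, one reference-based analysis.
- State the time levels of the diagnosis model and say how participants with no follow-up enter the analysis.
- Reword the aim so that it claims robustness to the stated departures from missing at random.

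Appendix B already schedules both questionnaires at every visit, so no new data are needed. The cost is SAP wording, some programming, the work of justifying the delta range, and one more results table.
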